### Randomization

Using a randomized blocked design function with a block size of four of R statistical software (version 2020) (36), participants will be randomly assigned to the TCFM or the placebo massage group in a one-to-one ratio. This will guarantee that up until the desired sample size is reached, each group will have roughly equal size of participants. The therapist will be informed of the group assignment after a participant gives consent to participate in the trial and the baseline data are collected. Since each participant's information will be de-identified, a unique ID number will be generated to represent the identity of that participant. The confidentiality of all participants' information will be maintained throughout and after the trial. Access will only be permitted to those who are authorized.

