### Recruitment

Two interventionists will be trained by the principal investigator on the recruitment protocol of this trial prior to the beginning of the trial. Flyers, officers' recommendations, sharing posts on Facebook, and the snowball method will be used to recruit PHIV from healthcare facilities at the Texas Medical Center in the US. People interested in the trial are encouraged to get in touch with the PI by phone or email to see if they qualify. Every interested respondent will have a phone or zoom conversation with the PI or the interventionists as an initial screening. The PI or the interventionists will inquire as to whether they experience any of PN symptoms in their lower extremity, such as numbness, decreased sensation to pinprick, prickling or tingling, lack of coordination and falling, muscle weakness, and extreme sensitivity to touch. If they exhibit PN symptoms in their lower extremity, the PI or the interventionists will schedule a time to meet them face-to-face at their home or a room provided by the University of Houston-Downtown, depending on their preferences and convenience. The PI or the interventionists will conduct a complete screening of the person against the inclusion and exclusion criteria when they meet in person, determine whether they are eligible for participation, and obtain informed consent if they are eligible and willing to participate in the trial. The PI, the interventionists, the outcome assessors, and the therapists will all wear facial masks throughout the trial to protect every person they meet.

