### Blinding

While participants, the statistician, and the outcome assessors will be blinded, the PI and the therapists will be aware of participants' group assignment. This trial is, therefore, double blinded. However, it is likely that participants will have the right guess about the type of massage they have received.

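### With a fixed, published block size of four and a PI who knows assignments and may also screen and consent, up to a third of allocations could be known before enrolment

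*Protocol article*

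**What the plan says.** Three sections of the protocol article bear on this.

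- **Randomization.** The list is produced "Using a randomized blocked design function with a block size of four", and "participants will be randomly assigned to the TCFM or the placebo massage group in a one-to-one ratio". One size is given, and no variation in size and no stratification is described. The only timing rule concerns the therapist: "The therapist will be informed of the group assignment after a participant gives consent to participate in the trial and the baseline data are collected".
- **Blinding.** Participants, the statistician and the outcome assessors are blinded, whereas "the PI and the therapists will be aware of participants' group assignment". The section does not say when the PI learns each assignment. It does not list the two interventionists on either side.
- **Recruitment.** "The PI or the interventionists will conduct a complete screening of the person against the inclusion and exclusion criteria", and the same people "determine whether they are eligible for participation, and obtain informed consent if they are eligible and willing to participate in the trial". Interested people are asked to contact the PI first, and appointments are arranged individually.

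**The concern.** Blocks of one known size let anyone who has seen the earlier assignments work out some of the later ones. Usually that does little harm, because those who know past assignments do not decide who enters next. Here the PI is given both roles.

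Someone who knows or suspects the next arm can, even without intent, bring an appointment forward, put it off, or judge a doubtful case differently. The arms may then differ in prognosis or in expectation of benefit. The three primary outcomes (SF-MPQ-2, LEFS and SF-36) are questionnaire scores. The article also concedes that participants will probably guess which massage they received. With participant blinding that weak, unpredictable allocation is one of the main protections left.

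**Working it through.** **1. The plan's own figure.** The article gives no predictability figure. Its sample size sets the number of blocks, so that was reproduced first. Inputs from the Sample size section: power 0.80, two-sided 0.05, SD 2, difference 1, correlation 0.8, and 25% dropout at post-baseline visits.

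- Without dropout: n = 2 × [SD × (z₀.₉₇₅ + z₀.₈₀) / difference]² = 2 × [2 × (1.960 + 0.842) / 1]² = 62.79 per arm.
- Inflation factor with baseline complete and 75% retained at both later visits: 0.8² + (1 − 0.8²)/0.75 = 0.64 + 0.48 = 1.12.
- 62.79 × 1.12 = 70.33, rounded up to **71 per arm, 142 in total**, as stated.
- 142 = 35 complete blocks of four, plus 2 participants.

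**2. Allocations that are certain.** A block with two of each arm has 6 orderings. An allocation is certain once one arm has used both its places.

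| Orderings | Number | Certain allocations |
|---|---|---|
| AABB, BBAA | 2 | third and fourth |
| ABAB, ABBA, BAAB, BABA | 4 | fourth only |

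- Expected per block: (2/6) × 2 + (4/6) × 1 = 1.333 of 4 = **33.3%**.
- By position in the block: 0, 0, 1/3, 1.
- In 142 participants: 35 × 4/3 = **46.7** (32.9%). The last two participants add none.
- Possible range: 35 (24.6%) if every block has one certain allocation, to 70 (49.3%) if every block has two.

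**3. Best guess.** Always guess the arm that is behind, and toss a coin when the arms are level. The chance of being right at positions 1 to 4 is 1/2, 2/3, 1/3 × 1 + 2/3 × 1/2 = 2/3, and 1. The sum is 2.833 of 4 = **70.8%**, against 50% by chance.

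**4. The PI's share of enrolment.** The article does not give it, so it is an assumption. The calculation takes the PI's recruits to be spread over block positions like everyone else's.

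| Assumed PI share | Expected certain allocations | Of 142 |
|---|---|---|
| 100% | 46.7 | 33% |
| 50% | 23.3 | 16% |
| one third | 15.6 | 11% |

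All rows also assume one unstratified list and a PI who learns each assignment, in order, before the next consent. If the PI learned nothing until enrolment closed, the number would be zero.

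**5. What other block schemes would do.** By the same enumeration, fixed blocks of 6 leave 25% certain (best guess 68.3%) and fixed blocks of 8 leave 20% (66.6%). Mixed sizes were simulated for a recruiter who knows which sizes are possible but not their order. About 5% are then certain with 4 and 6, and about 2% with 4, 6 and 8.

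**The case against.** The strongest reply is that one third is a ceiling and not a forecast. Recruitment is shared with two interventionists, and the article says that the PI will know assignments but not when. Both points stand, which is why the size is given as a range. The 50% and one-third rows are not firm lower limits either: the PI is the first contact for interested people, and so can influence the timing of entries that an interventionist later consents.

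A second reply is that a journal article need not describe concealment. That is true, and who generates or holds the list is not counted here. But a hidden list does not prevent deduction from known past assignments. The block size, the PI's awareness and the PI's recruiting role are all stated, not omitted. The one stated timing safeguard covers the therapist only.

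A third is that there is little discretion at entry. Self-reported symptoms are one of seven inclusion criteria, and the others, such as verified HIV diagnosis, age and language, are harder to bend. This limits selective exclusion but does not touch the timing of individually arranged visits.

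A fourth is that the outcomes are measured before randomization and analysed as change from baseline by MMRM. This partly addresses selection on measured severity. It does not address selection on unmeasured prognosis or expectation. No bias in the treatment effect and no inflation of the type I error has been estimated here.

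**Conclusion.** The point holds as a vulnerability. Followed as written, the plan lets a person who knows past assignments also decide on entry, under a block scheme that makes up to 33% of allocations certain (expected 46.7 of 142). The expected figure is about 23 or 16 if the PI enrols half or a third of participants. These figures rest on one unstratified list and on the PI knowing each assignment before the next consent. The article states neither.

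A reader might infer three stronger things that the document does not support:

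- That a third of allocations will be known in advance. This needs the PI to enrol everyone and to learn each assignment at once.
- That everyone who recruits can predict the next arm. The article does not say whether the interventionists learn assignments.
- That the result will be biased beyond repair. The article shows an opportunity for selection, not its occurrence, and the baseline measurements give partial protection.

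**What to change.** Make two changes in the Randomization, Blinding and Recruitment sections.

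1. Generate the list with randomly varying block sizes, for example 4, 6 and 8, and do not disclose the sizes to anyone who recruits.
2. Separate the roles. Either keep the PI unaware of running assignments until enrolment ends, or leave screening and consent to the interventionists and state that they are not told assignments.

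The second change is the essential one. Varied blocks make few allocations certain, but someone who sees past assignments can still guess better than chance.

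The cost is a change to the R call and a few sentences, submitted to the ethics committee as the Protocol amendments section provides. The PI gives up either running access to assignments or a screening role. Sample size and staffing do not change. If enrolment has begun, the change protects only allocations still to be made.

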### Sample size

The sample size per arm is calculated using longpower R package (a package for longitudinal data sample size calculation) (37, 38). For a longitudinal design with two arms (with allocation ratio = 1:1) focusing on the difference in change from baseline at the last visit in SF-MPQ-2 total score, with a power of 0.8 and significance level of 0.05 (two-sided), a dropout rate of 25% at post-baseline visits in both arms, a compound symmetric within-individual correlation matrix with an intraclass correlation coefficient of 0.8 in both arms, a standard deviation of 2 for change in score from baseline at last visit (assuming the same in both arms), and effect size of 1, the sample size per arm is 71 (142 in total).

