**Sample size:**

An estimated 142 participants in total, or 71 participants in each arm, will be needed for this trial.

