### Statistical analysis

We will summarize the characteristics of the participants at baseline by treatment arm using descriptive statistics. Specifically, we will use mean (standard deviation) for normal (or roughly normal) continuous data, and medians (25th percentile, 75th percentile) for non-normal continuous data, and frequency (percentages) for categorical data. The two-sample *t-*test and chi-square test (or Fisher's exact test, as appropriate) will be used to examine differences by the two arms at baseline.

The primary outcome will be assessed according to intention-to-treat (48) principles. We will use a mixed model for repeated measures (MMRM) (49) to model the change from baseline at each post*-*baseline visit in two arms, with each of the primary outcomes as dependent variable. For each of the outcome, using MMRM, we will compare the difference between the treatment vs. placebo arm in change in mean response from baseline at last visit. The likelihood-based MMRM can handle missingness in the responses when the responses are missing at random (50).

For the secondary outcome, we will calculate rates of recruitment (defined as the number of consented individuals divided by the number of eligible individuals), completion (defined as the percentage of completion at baseline and follow-up visits), adherence (defined as participants' completed sessions divided by the number of offered sessions), and adverse events (in two forms, total number and number per participant).

The statistician is not part of the research team and is not aware of the group assignment. All analyses will be performed using R statistical software (version 2020) (36). A two-sided *P*-value of 0.05 or less will be considered statistical significance.

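### The 71 per arm rests on a sizing model that differs from the planned change-from-baseline MMRM; on the stated inputs the power is about 73% to 78%, not 80%

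*Protocol article*

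**What the plan says.** The abstract gives the result: "An estimated 142 participants in total, or 71 participants in each arm, will be needed for this trial". The Sample size section under Materials and methods gives the derivation, made with the longpower R package. The design has "two arms (with allocation ratio = 1:1"), the calculation is "focusing on the difference in change from baseline at the last visit in SF-MPQ-2 total score", and it is made "with a power of 0.8 and significance level of 0.05 (two-sided"). The remaining inputs are "a dropout rate of 25% at post-baseline visits in both arms, a compound symmetric within-individual correlation matrix with an intraclass correlation coefficient of 0.8", "a standard deviation of 2 for change in score from baseline at last visit", and an effect size of 1. The section does not give the retention at each visit, and it does not say whether the correlation matrix covers two visits or three.

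The Primary outcome section sets two post-baseline assessments: at the sixth visit and 12 weeks later. The Statistical analysis section plans a "mixed model for repeated measures (MMRM) (49) to model the change from baseline at each" post-baseline visit and compares the arms at the last visit. It does not say whether baseline is a covariate.

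**The concern.** When the response is a change score, baseline is already inside it. A participant who misses both post-baseline visits has no change score and adds nothing to the comparison. If a quarter are missing at both visits, the sample size must therefore grow by the full 1/0.75 = 1.33. The printed 71 reflects an increase of only 1.12 over the no-dropout size, so the calculation recovers information from somewhere that the planned model does not have.

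At stake is the only power statement in the protocol. A reader who meets a null result will take it that the trial had 80% power for one point on the SF-MPQ-2 total.

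**Working it through.** **Inputs.** From the Sample size section: two-sided alpha 0.05 (z = 1.960), power 0.80 (z = 0.842), 1:1 allocation, SD 2, difference 1, correlation 0.8, dropout 25%. From the Primary outcome section: two post-baseline visits. I read the effect size as one raw point, because a standardised effect of 1 would need only 16 per arm.

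**Formulas.** With V the per-participant variance after allowing for dropout:
- n per arm = 2 × (1.960 + 0.842)² × V / difference²
- power at n per arm = Φ(difference / √(2V/n) − 1.960)
- V = SD² × φ, where φ is the dropout inflation for the last visit. When the earlier response has retention r1, the last visit has retention r2, and they correlate ρ, φ = ρ²/r1 + (1 − ρ²)/r2.

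Without dropout, n = 2 × 7.849 × 4 = 62.8, or 63 per arm.

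**Reproducing 71.** Two readings give it:
- *Three visits, baseline counted as a response, retention (1, 0.75, 0.75).* φ = 0.64/1 + 0.36/0.75 = 1.12, V = 4.48, n = 70.3, rounded up to 71; power at 71 is 80.4%.
- *Two post-baseline visits, retention (1, 0.75), change scores correlated 0.8.* φ is again 1.12 and n is 71.

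**Setting these against the text.** The first reading needs an outcome with SD 2 that correlates 0.8 with baseline. The text gives 2 as the SD of the change. The change at baseline is zero for everyone, so it cannot carry information about later change, and the planned MMRM has only post-baseline changes as responses. The second reading has nobody missing at the sixth visit, against "a dropout rate of 25% at post-baseline visits in both arms". It also needs 0.8 to be the correlation between change scores. If 0.8 belongs to the raw scores, compound symmetry implies (1 − 0.8)/(2 × (1 − 0.8)) = 0.5 between changes. Then φ = 0.25 + 0.75/0.75 = 1.25, n = 78.5 (79 per arm), and power at 71 is 76.0%.

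**The planned model with 25% missing at both post-baseline visits.**
- *Change-score MMRM as written.* φ = ρ²/0.75 + (1 − ρ²)/0.75 = 1.333 for any ρ. V = 5.333, n = 83.7, or 84 per arm. Power at 71: 1/√(2 × 5.333/71) = 2.580, and Φ(2.580 − 1.960) = 73.2% (72.4% using the t distribution). Difference with 80% power: √(83.7/71) = 1.09.
- *Baseline as covariate, 0.8 as the raw-score correlation.* Raw variance = 4/(2 × 0.2) = 10; residual variance = 10 × (1 − 0.64) = 3.6; V = 3.6/0.75 = 4.8; n = 75.4, or 76 per arm. Power at 71 is 77.6%. Difference with 80% power: √(75.4/71) = 1.03.
- *Raw scores at all three visits, unconstrained baseline, change contrast.* V = 10 × (0.36/0.75 + 0.04) = 5.2; n = 81.6, or 82 per arm. Power at 71 is 74.3%.

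None of the three reaches 80%.

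**The case against.** The strongest reply is that 71 is not a miscalculation. It comes out of the standard MMRM formula with the printed alpha, power, SD, difference, correlation and dropout once baseline is entered as a visit. That stands: a reader might infer an arithmetic error, and the document does not support this.

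A second reply is that 73% belongs to one model. A condensed article may leave the covariate list to a fuller document, and baseline adjustment is common. That also stands, which is why the result is a range. The retention at each visit is not printed either. If dropout builds up evenly, with retention (0.875, 0.75), the change-score model at 71 per arm has 77.2% power when changes correlate 0.8 and 74.8% when they correlate 0.5. With baseline adjustment and nobody missing at the first post-baseline visit it has 79.7%, which is 80% for practical purposes, but that retention is not what the text describes.

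A reader might go further. If 0.8 is the raw-score correlation, an SD of change of 2 implies a raw SD of √10 = 3.16, which is wide for a 0 to 10 scale. From this one might infer that 2 was really the SD of the score and that the trial is larger than it needs to be. The document does not support that. It expressly assigns the 2 to the change, it does not say which scores the correlation describes, and 3.16 is possible on a scale where the SD can reach 5. Nor does it support reading the 25% as a fresh loss compounded at each visit.

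**Conclusion.** The point holds as a mismatch between the model used for sizing and the model planned for analysis. On the stated SD of change of 2, a difference of 1 and 25% missing at both post-baseline visits, 71 per arm gives about 73% power for the change-score MMRM as written and about 78% with baseline as a covariate, against a stated 80%. The shortfall is roughly 2 to 7 percentage points.

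This rests on three assumptions: the effect size is one raw point; the same quarter of participants is missing at both visits; and, for the 78% only, 0.8 is the correlation between raw scores. The 73% does not depend on the correlation. I tried the readings shown here and found two that return 71; others may exist that the article does not print.

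The consequence is modest. No test or analysis changes, and the detectable difference moves from 1 to between 1.03 and 1.09. The statement should be corrected, but the trial's design does not depend on the correction.

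**What to change.** Keep 142 participants. In the Sample size section:
- state the retention assumed at each of the two post-baseline visits, and whether baseline is a row of the correlation matrix;
- state which scores the correlation of 0.8 and the SD of 2 describe;
- say whether the MMRM adjusts for baseline, in the same words as the Statistical analysis section, and rerun the calculation for that model;
- report the result, either as power for one point (about 73% unadjusted, about 78% baseline-adjusted, on the inputs now stated) or as the difference detectable with 80% power (1.09 or 1.03).

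The cost is one reworded paragraph and a slightly less favourable power statement. No further participants or visits are needed.

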### Blinding

While participants, the statistician, and the outcome assessors will be blinded, the PI and the therapists will be aware of participants' group assignment. This trial is, therefore, double blinded. However, it is likely that participants will have the right guess about the type of massage they have received.

### The TCFM (Tui Na)

Participants in the TCFM group will receive 6 weekly 25-min TCFM sessions provided by a therapist. The therapist will begin each session with an assessment of the legs and toes of the affected extremity for broken skin and lesions that would identify areas at risk for irritation during the massage and need to be avoided. The participant will be positioned with support to their foot and legs, with the sole of the foot plantar flexed and the therapist directly in alignment with the foot. The therapist will serially perform the following four steps for each TCFM session.

#### Step one: Releasing the channel sinews

One finger-pressing massage and vibration will be applied along the lower extremity points Gall Bladder Channel (39) points Qiuxu (GB40), Juegu (GB39), Yangfu (GB38), Guangming (GB37), Waigu (GB36), Yangjiao (GB 35), and Yanglingquan (GB34) using the thumb tip of the dominant hand of the therapist. All pressing and vibration maneuvers will be repeated for three rotations along the above identified GB channel of 60 s per point with the same repeated sequence along the channel. The vibrating massage will deliver 50 strokes for 30 s per point to release the sinews.

#### Step two: Stimulating the AhShi, along with breaking up and dispersion of stagnations

During the finger-pressing massage, the therapist will identify any sensitive areas, trigger points, contracted muscle areas, and nodules. As those areas are identified during one finger-pressing procedure, additional time will be spent to elicit a therapeutic response of change in sensation. The AhShi points will be treated with deeper penetrating pressure to surrounding the dragon (a local treatment using intense energy around the affected area) using vibration. The stagnation will be further dispersed with consistent pressure to the center of AhShi with the whorled surface of the thumb.

#### Step three: Moving and invigorating the flow of Qi and blood

A rolling technique will be applied for three passes from the heel to the toes to invigorate Qi flow. The rolling will be concluded with pressing and vibrating manipulation with the interphalangeal joint of the middle finger of the therapist to the participant's Yongquan (KI 1) acupoint. Step 3 will be repeated three times on the plantar surface of the foot.

